### Sample size estimation

The sample size calculation was based on an internal pilot dataset (n = 30) collected at the coordinating center prior to trial registration, using the minimal knee flexion angle during the swing phase on the hemiparetic side as the primary outcome measure. The pilot study was approved by the Medical Ethics Committee of the Affiliated Changshu Hospital of Soochow University (Approval No. X202265), and pilot participants were not included in the current trial (19). The use of pilot data to inform feasibility and parameter estimates for subsequent studies is supported by methodological guidance on pilot studies and pilot-informed trial planning (19, 20).

In the pilot dataset, the mean pre–post change in the primary outcome was 1.2 degrees, with a standard deviation of the within-subject change score of 6.36. The standardized effect size was therefore d = 0.1887 (d = Δμ/SDΔ). Although the pilot-derived effect size was small, the minimal knee flexion angle represents a joint-level biomechanical marker of neuromuscular coordination (21). Variations in swing-phase knee flexion primarily reflect changes in limb advancement mechanics and inter-joint coordination rather than global functional performance. Therefore, even relatively small angular differences may provide meaningful biomechanical information relevant to post-stroke gait recovery. Sample size estimation was performed using G*Power (difference between two dependent means, matched pairs). With an effect size (dz) of 0.1887, a one-sided significance level (*α*) of 0.05, and statistical power (1−β) of 0.80, the required minimum sample size was calculated to be 174 patients. A one-sided test was adopted, given the directional hypothesis that GCST would improve, rather than worsen gait performance. To account for potential attrition and to ensure balanced recruitment across centers, the planned recruitment target was set at 180 participants across four participating centers (approximately 45 participants per center). Based on pilot observations and adherence-enhancing procedures implemented in the study protocol, the anticipated attrition rate is expected to remain low. Healthy controls were not included in the sample size calculation and were recruited solely to provide normative reference values.

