### Assessment and follow-up

Biomechanical assessment equipment is calibrated according to manufacturer guidelines prior to each testing session. Calibration logs are maintained at each center to ensure measurement consistency. Assessments will be conducted at baseline, after the completion of each step, and during semi-annual and annual follow-ups post-treatment. The primary outcome of this study is the minimal knee flexion angle of the hemiparetic limb during the swing phase of gait, measured by three-dimensional gait analysis. This parameter is defined as the lowest knee flexion value observed in the swing phase of each gait cycle and reflects dynamic knee extension control during limb advancement. Reduced knee flexion during swing is a defining biomechanical feature of post-stroke stiff-knee gait and has been consistently associated with impaired toe clearance, altered limb advancement, and compensatory strategies such as hip circumduction and contralateral vaulting (22, 23). From a neuromechanical perspective, insufficient swing-phase knee flexion is linked to abnormal muscle activation patterns, particularly prolonged quadriceps activity and disrupted inter-joint coordination, making this parameter sensitive to lower-limb neuromuscular integration and rehabilitation-induced changes (21, 24) Table 1 presents a detailed schedule of the assessments and the responsible centers.

**Table 1 tab1:** Schedule of assessments and measurement time points.

Timepoint* Assessments^#^	t_0_, t_0*_	t_1_	t_2_	t_3_	t_4_	t_5_	t_6_
MA	√○□	√○□	√○□	√○□	√○□		
sEMG	√	√	√	√	√		
COP	□	□	□	□	□		
PPD	√□	√□	√□	√□	√□		
PS	□	□	□	□	□		
3DGA	√○	√○	√○	√○	√○		
BRS	√○□	√○□	√○□	√○□	√○□		
FMA-LE	√○□	√○□	√○□	√○□	√○□		
FAC	√○□	√○□	√○□	√○□	√○□	√○□	√○□
SLS	√○□	√○□	√○□	√○□	√○□		
BBS	□	□	□	□	□		
MMT	√○□	√○□	√○□	√○□	√○□		
MAS	√○□	√○□	√○□	√○□	√○□		
SF-36	√○□	√○□	√○□	√○□	√○□	√○□	√○□
BI	√○□	√○□	√○□	√○□	√○□	√○□	√○□
TEAE		√○□	√○□	√○□	√○□	√○□	√○□

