Time points: t_0_: Baseline (patients); t_0*_: baseline (healthy controls); t_1−_ t_4_:post-step assessments (after the completion of steps B–E, respectively); t_5_: semi-annual follow-up; t_6_: annual follow-up. MA, muscle architecture; sEMG, surface electromyography; COP, center of pressure; PPD, plantar pressure distribution; PS, postural sway; 3DGA, three-dimensional gait analysis; BRS, Brannstrom recovery stage; FMA-LE, Fugl–Meyer Lower Extremity; FAC, functional ambulation category; SLS, single-leg stance; BBS, Berg Balance Scale; MMT, manual muscle testing; MAS, Modified Ashworth Scale; SF-36, 36-Item Short Form Health Survey; BI, Barthel Index; TEAE, treatment-emergent adverse event; Center indicators: √, Suzhou and Kunshan sites; ○, Changshu site; □, Zhangjiagang site.

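### Table 1 schedules no 3DGA at Zhangjiagang, yet about 45 participants there count towards the 174 needed for the 3DGA-based primary outcome; if Table 1 is complete, power is about 0.70, not 0.80

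*Protocol article*

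**What the plan says.** Three statements in the protocol article bear on this.

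- **Source of the primary outcome (Assessment and follow-up).** It is "the minimal knee flexion angle of the hemiparetic limb during the swing phase of gait, measured by three-dimensional gait analysis". The abstract agrees, and no other instrument is named as a source for it.
- **Where each assessment is done (Assessment and follow-up, Table 1).** The text introduces the table with "Table 1 presents a detailed schedule of the assessments and the responsible centers". In the legend the tick stands for the first two sites and the other symbols follow: "Suzhou and Kunshan sites; ○, Changshu site; □, Zhangjiagang site". The 3DGA row carries √○ at t0 to t4 and never □.
- **How many are needed and where they come from (Sample size estimation).** From a paired comparison on this angle, "the required minimum sample size was calculated to be 174 patients". The text then says that "the planned recruitment target was set at 180 participants across four participating centers (approximately 45 participants per center"). All four centres are counted, Zhangjiagang included.

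**The concern.** The figure of 174 comes from a paired-means calculation on the knee angle. It is therefore the number of people who must have a before and an after value from 3DGA, not merely the number enrolled. If one of four equally sized centres does no 3DGA, about a quarter of those enrolled cannot contribute. The allowance of 180 over 174 is six people, or 6/180 = 3.3%, which is far too small to cover that.

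At stake is the stated power for the trial's only primary outcome. There is also a modelling consequence. The Statistical analysis section enters centre as a fixed effect, and the effect of a centre with no outcome values cannot be estimated.

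**Working it through.** **Inputs, all from Sample size estimation unless noted**

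- Mean change: "the mean pre–post change in the primary outcome was 1.2 degrees"
- SD of change: "standard deviation of the within-subject change score of 6.36"
- dz = 1.2/6.36 = 0.1887
- Paired test, one-sided alpha 0.05, target power 0.80
- Stated minimum 174; recruitment target 180; about 45 per centre at four centres
- Centres with 3DGA: three of four (Table 1 and its legend)

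**Step 1. Reproduce the plan's figure.**

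Normal approximation: n = ((z0.95 + z0.80)/dz)² = ((1.645 + 0.842)/0.1887)² = 173.6, rounded up to 174.

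The exact paired t test has power = P(T > t0.95, n−1), where T is noncentral t with n−1 degrees of freedom and noncentrality dz·√n. The smallest n reaching 0.80 is 175, and n = 174 gives 0.798. The stated 174 is reproduced within rounding. The two-sided version would need 223, so the one-sided setting was the one used. The arithmetic of the sample size is sound.

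**Step 2. Read Table 1.** The symbols are used consistently:

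| Rows | Symbols | Centres |
|---|---|---|
| MA, BRS, FMA-LE, SLS, MMT, MAS | √○□ | all four |
| COP, PS, BBS | □ | Zhangjiagang only |
| sEMG | √ | Suzhou and Kunshan |
| 3DGA | √○ | Suzhou, Kunshan, Changshu |

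The 3DGA pattern is the same at all five time points, so a typing slip or damage in reading the PDF is unlikely.

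**Step 3. Number able to supply the outcome.** 3 × 45 = 135, that is 135/180 = 75%. Since 45 is approximate, I take 125 to 144 in total (about 42 to 48 per centre) as an assumed range.

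**Step 4. Power on the plan's own basis (dz 0.1887, one-sided 0.05).**

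| n with paired values | Noncentrality dz·√n | Power |
|---|---|---|
| 180 | 2.53 | 0.810 |
| 174 | 2.49 | 0.798 |
| 144 | 2.26 | 0.729 |
| 135 | 2.19 | 0.704 |
| 130 | 2.15 | 0.690 |
| 125 | 2.11 | 0.675 |

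The normal approximation at 135 gives 0.708. The row for 130 is 135 less the 3.3% margin implied by 180 against 174; the article gives no attrition rate beyond calling it low.

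**Step 5. Detectable change at n = 135.** Solving for 80% power gives dz = 0.2151, and 0.2151 × 6.36 = 1.37 degrees.

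**Step 6. Does the analysis model help?** The likelihood approach in Statistical analysis brings in people with some but not all values. Someone with no value of the outcome at any visit, baseline included, contributes nothing to the likelihood for that outcome and so nothing to the time effect.

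**The case against.** **Testing at another centre.** Table 1 is said to list responsible centres, which could mean the centre that performs a test rather than the centre whose patients receive it. All four hospitals are in Suzhou, and the ethics section allows reimbursement of travel. On that reading Zhangjiagang participants might go elsewhere for 3DGA and no power would be lost. The reading is weak: recruitment is of inpatients, no transfer for 3DGA is described, and the rows marked for all centres suggest that each site tests its own patients. But it is not excluded. A reader might therefore infer as fact that the outcome is never measured in Zhangjiagang participants. The documents do not go that far, and the power loss has to be stated as conditional on Table 1 being complete.

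**Missing at random.** A reader might also infer that a wholly unmeasured centre breaks the missing-at-random assumption. It does not follow. Missingness determined by centre depends on an observed variable that is already in the model, which is compatible with that assumption. The difficulty is lack of information, not the missingness mechanism.

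**Basis of the power figure.** The planned analysis is a repeated-measures mixed model, not a paired t test, and its power may differ. That is fair, but the article gives no inputs for such a calculation and justifies its size only by the paired test.

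**Left to the full protocol or analysis plan.** This does not answer the point. It concerns two published sections that disagree, not a detail omitted.

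**Conclusion.** The point stands as an inconsistency between Table 1 and the recruitment plan. It is not an error in the sample size arithmetic, which reproduces.

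As printed, the schedule does not deliver the number of primary-outcome measurements on which the stated power rests. If Table 1 is complete and each site tests its own patients, power is about 10 percentage points below the stated 0.80, before any attrition.

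This rests on roughly equal recruitment across centres, the pilot effect size and SD, and the plan's one-sided paired test. Every value in the assumed range of 125 to 144 falls short of 0.80. If Zhangjiagang participants are in fact measured, the loss disappears, but the text still needs correcting.

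**What to change.** Reconcile Sample size estimation with Table 1. First establish whether Zhangjiagang participants undergo 3DGA.

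1. **If they do**, on site or at another centre, state this in Assessment and follow-up and correct the 3DGA row of Table 1. The cost is a line of text, and the stated power can stay.
2. **If they do not**, state that the primary analysis set is the participants at the three 3DGA centres (about 135), and restate power as about 0.70 for 1.2 degrees, or 80% for about 1.37 degrees. Say also that the centre effect for this outcome covers three centres. The cost is a less favourable stated power.

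Spreading the 180 over the three 3DGA centres is not a free alternative. At 60 each, 3 × 60 = 180 leaves nobody at Zhangjiagang, and COP, PS and BBS, which Table 1 assigns to that centre alone, would then be measured in no one.

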### Patient and public involvement

The patients and public involvement informed the study’s development, integrating feedback to align the design, methods, and implementation with the needs of the patients and the public. During pilot implementation, informal feedback was obtained from stroke patients regarding session tolerance and assessment burden. Participants reported increased fatigue during prolonged standing tasks and expressed a preference for structured rest intervals. In response, the session duration was standardized within a tolerable range. The order of biomechanical assessments was also adjusted to minimize cumulative fatigue.

### Intervention

Physicians will enroll hemiparetic stroke patients in the recovery and chronic phases for GCST treatment. Healthy controls will undergo a single assessment session without intervention. Healthy controls are included to establish normative reference values for gait kinematics and neuromuscular parameters. Their data will serve as a benchmark for quantifying baseline deviations from typical gait patterns in the stroke cohort and for contextualizing longitudinal changes observed during follow-up. Changes in the stroke cohort will be compared with normative values to evaluate the degree to which gait parameters converge toward typical movement patterns over time.

All participating therapists must have at least 3 years of clinical experience in neurological rehabilitation. Prior to study initiation, therapists will undergo a centralized GCST training workshop including theoretical instruction, demonstration of each intervention step (A–E), supervised practice sessions, and competency assessment. Certification requires the successful completion of a standardized checklist and the demonstration of correct procedural execution. Refresher training sessions are conducted quarterly. Therapists will administer the GCST program, which involves 30-min daily sessions, five times per week. The GCST steps are illustrated in Figure 3.

**Figure 3 fig3:**
[figure not shown]
Diagram of the GCST steps.

Given that all participants are unilateral hemiparetic, the training commences at step B. Each step utilizes overlapping motor tasks and incremental difficulty to progressively unlock the patients’ potential. Progression from one GCST step to the next is based on predefined performance criteria rather than therapist discretion. Upon passing the step E test, the treatment cycle is concluded. Throughout the treatment, the number of days taken to complete each step is recorded. Each step is implemented at the patient’s maximum tolerable intensity. Once the criteria for progression are met, the next step is initiated immediately. Specific operational details are provided in Figure 2. Intervention sessions are terminated if participants experience dizziness, excessive fatigue (Borg scale > 15), unstable blood pressure, pain exacerbation, or an inability to maintain a safe standing posture. Safety monitoring is performed continuously during training. To ensure treatment fidelity across centers, a standardized intervention manual has been developed. Sessions are documented using structured fidelity checklists. A random 10% of sessions are video recorded (with patient consent) and reviewed by an independent senior investigator. Deviations from the protocol are documented, and corrective feedback is provided.

All hemiparetic stroke patients will receive conventional treatments based on clinical guidelines. They can participate in upper-extremity training, sitting balance exercises, lying-position training, stretching programs, and physical therapy as needed. However, strength training or motor skill training related to standing and gait functions is expressly excluded.

### Assessment and follow-up

Biomechanical assessment equipment is calibrated according to manufacturer guidelines prior to each testing session. Calibration logs are maintained at each center to ensure measurement consistency. Assessments will be conducted at baseline, after the completion of each step, and during semi-annual and annual follow-ups post-treatment. The primary outcome of this study is the minimal knee flexion angle of the hemiparetic limb during the swing phase of gait, measured by three-dimensional gait analysis. This parameter is defined as the lowest knee flexion value observed in the swing phase of each gait cycle and reflects dynamic knee extension control during limb advancement. Reduced knee flexion during swing is a defining biomechanical feature of post-stroke stiff-knee gait and has been consistently associated with impaired toe clearance, altered limb advancement, and compensatory strategies such as hip circumduction and contralateral vaulting (22, 23). From a neuromechanical perspective, insufficient swing-phase knee flexion is linked to abnormal muscle activation patterns, particularly prolonged quadriceps activity and disrupted inter-joint coordination, making this parameter sensitive to lower-limb neuromuscular integration and rehabilitation-induced changes (21, 24) Table 1 presents a detailed schedule of the assessments and the responsible centers.

**Table 1 tab1:** Schedule of assessments and measurement time points.

Timepoint* Assessments^#^	t_0_, t_0*_	t_1_	t_2_	t_3_	t_4_	t_5_	t_6_
MA	√○□	√○□	√○□	√○□	√○□		
sEMG	√	√	√	√	√		
COP	□	□	□	□	□		
PPD	√□	√□	√□	√□	√□		
PS	□	□	□	□	□		
3DGA	√○	√○	√○	√○	√○		
BRS	√○□	√○□	√○□	√○□	√○□		
FMA-LE	√○□	√○□	√○□	√○□	√○□		
FAC	√○□	√○□	√○□	√○□	√○□	√○□	√○□
SLS	√○□	√○□	√○□	√○□	√○□		
BBS	□	□	□	□	□		
MMT	√○□	√○□	√○□	√○□	√○□		
MAS	√○□	√○□	√○□	√○□	√○□		
SF-36	√○□	√○□	√○□	√○□	√○□	√○□	√○□
BI	√○□	√○□	√○□	√○□	√○□	√○□	√○□
TEAE		√○□	√○□	√○□	√○□	√○□	√○□

Time points: t_0_: Baseline (patients); t_0*_: baseline (healthy controls); t_1−_ t_4_:post-step assessments (after the completion of steps B–E, respectively); t_5_: semi-annual follow-up; t_6_: annual follow-up. MA, muscle architecture; sEMG, surface electromyography; COP, center of pressure; PPD, plantar pressure distribution; PS, postural sway; 3DGA, three-dimensional gait analysis; BRS, Brannstrom recovery stage; FMA-LE, Fugl–Meyer Lower Extremity; FAC, functional ambulation category; SLS, single-leg stance; BBS, Berg Balance Scale; MMT, manual muscle testing; MAS, Modified Ashworth Scale; SF-36, 36-Item Short Form Health Survey; BI, Barthel Index; TEAE, treatment-emergent adverse event; Center indicators: √, Suzhou and Kunshan sites; ○, Changshu site; □, Zhangjiagang site.

### Outcome measures

Muscle architecture

Muscle thickness and structural characteristics of 22 lower-extremity muscles will be assessed using high-frequency ultrasound (X-Porte TTC). These muscles include bilateral gluteus maximus, gluteus medius, gluteus minimus, rectus femoris, vastus medialis, vastus lateralis, vastus intermedius, popliteus, long head of the biceps femoris, short head of the biceps femoris, semitendinosus, and semimembranosus. Restoration of muscle thickness symmetry has been shown to correlate with improved muscle strength (25).

2. Surface electromyography indicators

Using the Noraxon Ultium wireless surface electromyography system (Noraxon, Scottsdale, AZ, USA), in accordance with European Surface EMG for non-invasive assessment of muscles (SENIAM) guidelines (26), 16 wireless sEMG electrodes are placed on the bilateral gluteus maximus, gluteus medius, rectus femoris, vastus medialis, biceps femoris, tibialis anterior, medial gastrocnemius, and soleus muscles. Signals are synchronously recorded at a sampling rate of 2,000 Hz. A fourth-order Butterworth bandpass filter (20–500 Hz) is applied to eliminate low-frequency noise and high-frequency interference, and a notch filter is used to remove 50 Hz power-frequency interference. Data are collected during the Achilles tendon reflex, standing, and walking tasks to calculate muscle frequency-domain characteristics and non-linear network indicators (11).

3. Postural parameters

Center of Pressure: A balance test and training device (ProKin 254, TecnoBody, Italy) is utilized to assess balance during bipedal stance. The static load test is conducted with a three-dimensional force platform (Advanced Mechanical Technology, Inc., BMS400600, USA) to quantify forces and torques in a stationary state.

Plantar Pressure Distribution: A pressure distribution measurement platform (Sensor Medica, FM30050, Italy) is utilized to measure pressure distribution, contact area, and center position.

Postural Sway: The APDM system (Opal sensors, Mobility Lab v2) is used to measure the postural sway during standing with eyes open and closed. Sensors are fixed on both wrists, the dorsum of both feet, the xiphoid process of the sternum, and the L_5_ spinous process for a 30-s test (27). It can detect 33 postural-sway parameters, including 25 acceleration parameters and 8 angular parameters.

4. Gait parameters

Three-Dimensional Gait Analysis: A three-dimensional motion capture system (Vicon, Vero 2.2, UK) is used to collect kinematic and dynamic parameters during walking. Reflective markers are placed on the body based on the Full-Body Gait Model (28). Data collection is performed using Vicon Nexus. After data collection, the Polygon report analysis software is used to calculate fundamental spatiotemporal parameters, joint angles, and moments during gait, focusing on key joints such as the knees and hips. A three-dimensional force platform (Advanced Mechanical Technology, Inc., BMS400600, USA) captures real-time force and pressure changes throughout the gait cycle, enabling the calculation of joint moments, joint forces, and dynamic characteristics of gait (29). Simplified gait tests using the APDM system (Opal sensors, Mobility Lab v2) are conducted to detect 40 gait parameters, including 4 arm parameters, 6 axial parameters, 20 lower-extremity motion parameters, and 10 gait cycle ratios.

5. Lower-extremity motor function

The Brunnstrom Recovery Stage assessment is used to assess motor recovery in post-stroke patients, dividing the recovery process into stages from no spontaneous movement to the ability to perform complex movements independently (30). The Fugl–Meyer Lower-Extremity scale evaluates lower-extremity motor control in post-stroke patients, covering strength, muscle tone, range of motion, and coordination. An FMA-LE score of 21 or higher indicates a higher level of functional mobility (31), while an increase of 6 points suggests a significant improvement in rehabilitation outcomes (32). The Functional Ambulation Category assesses patients’ walking ability in various environments to determine their independence and stability in daily activities (33). Single-leg stance quantifies balance ability by recording the longest standing time over three trials, performed under both eyes-open and eyes-closed conditions (34). The Berg Balance Scale, which includes 14 dynamic and static tasks, comprehensively assesses balance function. A total score below 40 indicates a risk of falls (35). Manual Muscle Testing is used to evaluate the strength of the gluteus maximus, gluteus medius, quadriceps, hamstrings, tibialis anterior, gastrocnemius, and soleus muscles using a 5-point scoring system (36). The Modified Ashworth Scale assesses muscle tone of the knee extensors and ankle plantar flexors, with 0 indicating no resistance and 4 indicating significant stiffness during flexion or extension (37).

6. Quality of life

The 36-Item Short Form Health Survey is a highly reliable and valid questionnaire that is widely accepted for its ease of use. It includes eight dimensions, such as physical functioning, social functioning, pain, and vitality, making it suitable for evaluating quality of life across various diseases (38). The Barthel Index measures functional independence in activities of daily living. It comprises 10 items related to daily living activities, with a total score of 100 points; higher scores indicate greater independence in daily life (39).

